#### Interim analyses {21b}

The efficacy and safety of the Val/Aml combination have been demonstrated in large randomized controlled trials. In addition, the research treatment period was set to only 4 weeks. Therefore, we have no interim analyses or stopping guidelines.

### Methods for additional analyses (e.g., subgroup analyses) {20b}

We will consider whether to conduct subgroup analysis according to the subject’s age, BMI, and so on.

### Methods in analysis to handle protocol non-adherence and any statistical methods to handle missing data {20c}

Statistical analysis will be based on the ITT and PP principles. In ITT analyses, missing data will be supplemented by the last observation carried forward (LOCF) method.

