#### Suspension criteria

The following are the suspension criteria:
Poor compliance of patients.The mean sitting SBP (msSBP) ≥ 200 mmHg and/or the mean sitting DBP (msDBP) ≥ 120 mmHg will result in exclusion at any time during the study period.Adverse events (AEs), complications, or physiological changes that are fatal.Use of prohibited drugs or treatments that may affect the analysis of results during the trial.Voluntary withdrawal.Incomplete data.Withdrawal due to various reasons, such as failure to participate in the follow-up.

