**Biochemical index**		
Blood lipids	On days 0 and 28 of the treatment cycle, the researchers will collect the morning fasting blood of each subject for biochemical detection.	0,28
Blood sugar		
Urine microalbumin		
Uric acid		
Homocysteine		
C-reactive protein		

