#### Sample size {14}

The trial will check for superiority between the treatment group (treatment with Val/Aml and TJT) and the control group (treatment with Val/Aml and TJT placebo).

The calculation of sample size is based on the hypothesis of superiority and the method of comparing the two means. Assuming that the class I error rate is *α* = 0.05 and the class II error rate is *β* = 0.2, and based on a previous study [19], the test group DBP after treatment (*πc*) can be set as follows: DBP, 8.3 ± 5.53 mmHg, and the control group DBP after treatment (*πt*) can be set as follows: DBP, 6.3 ± 4.31 mmHg based on the effectiveness test sample size calculation formula:
$$ N=\left[2{\left({Z}_{1-\alpha }+{Z}_{1-\beta}\right)}^2{\delta}^2\right]/{\left({\pi}_T-{\pi}_c\right)}^2 $$

**δ**^2^ = (S1^2^ + S2^2^)/2; S1 and S2 are the standard deviations of the control group and treatment group, respectively; *α* = 0.05, *Z*_1−*α*_ = 1.96, *β* = 0.1, *Z*_1-*β*_ = 1.28, (*Z*_1 − *α*_ + *Z*_1 − *β*_)^2^ = 6.2. Then, each group needs a sample size of 120. The quality of the study will be strictly controlled during the trial. After considering the Good Clinical Practice (GCP) shedding rate (20%) and expanding the number of samples, we decided to recruit 288 patients in this trial, including 144 patients in the treatment group and 144 patients in the control group. The total number of cases in the two combinations will be 288: 144 in the treatment group and 144 in the control group.

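### LOCF is the only missing-data method for the ITT analysis: it always imputes zero change for the syndrome score and biochemistry, dilutes a real blood pressure effect, and can bias it either way if loss differs by arm

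*Protocol article*

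**What the plan says.** The section on protocol non-adherence and missing data {20c} sets the analysis sets and the imputation rule: "Statistical analysis will be based on the ITT and PP principles", and then "In ITT analyses, missing data will be supplemented by the last observation carried forward (LOCF) method". The ITT set is all consented and randomised subjects. The PP set is those who complete according to protocol. No other way of handling missing values is given.

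The Sample size section {14} provides for loss: "After considering the Good Clinical Practice (GCP) shedding rate (20%) and expanding the number of samples", leading to 144 per arm.

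The primary outcomes are the changes in msSBP and msDBP from baseline to week 4. Table 1 lists blood pressure on days 0, 3, 14, 21 and 28. Study setting {9}, Participant timeline {13} and Plans for assessment {18a} all make day 3 and week 3 telephone contacts, with on-site visits at weeks 2 and 4 only. Table 1 puts the syndrome score on days 0 and 28. For biochemistry it says "On days 0 and 28 of the treatment cycle".

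The Suspension criteria list reasons for leaving the study. They include poor compliance, prohibited drugs, incomplete data, a blood pressure threshold that "will result in exclusion at any time during the study period", and "Withdrawal due to various reasons, such as failure to participate in the follow-up". The unblinding section {17b} has unblinded subjects discontinue the study.

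**The concern.** LOCF assumes that nothing changes after the last reading. Here both arms begin an active antihypertensive combination at randomisation, and the planning values are themselves falls in blood pressure. A patient who leaves early is therefore scored at a value the design expects to be too high.

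For outcomes with only a baseline and a final measurement, LOCF is baseline carried forward without exception. A drop-out's efficacy index on the syndrome score becomes 0%, which falls in the protocol's category for no response.

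Several suspension criteria depend on blood pressure, tolerability or adherence, so loss may differ by arm in amount or timing. The treatment difference can then move in either direction, and LOCF cannot be defended as reliably conservative. It also treats filled-in values as if they had been observed.

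**Working it through.** **The plan's own figures.** The step to 144 per arm is 120 × 1.2 = 144. The 120 itself is not reproduced by the printed inputs: factor 6.2 gives 2 × 6.2 × 24.58 / 4 = 76.2, and (1.96 + 1.28)² = 10.50 gives 129.0. That is a separate matter and nothing below depends on it. At 20% loss, 144 × 0.20 = 28.8, so about 29 patients per arm would be imputed and about 115 observed.

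**Inputs from the Sample size section.** DBP 8.3 (SD 5.53) on TJT and 6.3 (SD 4.31) on control, read as reductions because they cannot be DBP levels. Pooled SD = √((5.53² + 4.31²)/2) = 4.96. Two-sided α = 0.05 and a two-sample comparison, from the statistical methods section. No planning values are given for SBP, so the figures are for DBP only.

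**Assumptions not in the documents.** The split of loss between arms; the timing of loss; 80% of the fall reached by day 14; the same SD at day 14 as at day 28; loss unrelated to the individual response within an arm.

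**Day 0 and 28 outcomes.** Change = baseline − baseline = 0 for every drop-out. The efficacy index is (points before − points after)/points before = 0%, below the 30% cut-off. This needs no assumption about timing.

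**Blood pressure.** Let e be the proportion lost with baseline only, l the proportion lost after day 14, f = 0.8, and m and s the mean and SD of the fall. Under LOCF:

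- mean = (1 − e − l + f·l)·m
- variance = (1 − e)·s² + (1 − e − l + f²·l)·m² − mean²

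With no loss, 144 per arm gives 2.00 mmHg and 92.8% power.

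Example, 20% loss in both arms, all with baseline only:

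- TJT: mean 0.8 × 8.3 = 6.64; variance 0.8 × (30.58 + 68.89) − 44.09 = 35.49
- Control: mean 0.8 × 6.3 = 5.04; variance 0.8 × (18.58 + 39.69) − 25.40 = 21.21
- Difference 1.60; SE = √((35.49 + 21.21)/144) = 0.627; power = Φ(1.60/0.627 − 1.96) ≈ 72%

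Planned effect 2.0 mmHg, 20%/20% loss:

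| Timing of loss | Multiplier of m | LOCF difference | Power |
|---|---|---|---|
| All with baseline only | 0.80 | 1.60 | 72% |
| Half with baseline only | 0.88 | 1.76 | 82% |
| All after day 14 | 0.96 | 1.92 | 90% |

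For comparison, 115 completers per arm with ignorable loss have 86% power.

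No true effect (both arms fall 6.3 mmHg), 15% loss on TJT and 25% on control:

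| Timing of loss | Multipliers TJT / control | False difference | Type I error, SD 4.96 |
|---|---|---|---|
| All with baseline only | 0.85 / 0.75 | 0.10 × 6.3 = 0.63 | 18% (21% at SD 4.31) |
| Half with baseline only | 0.91 / 0.85 | 0.06 × 6.3 = 0.38 | 10% |
| All after day 14 | 0.97 / 0.95 | 0.02 × 6.3 = 0.13 | 5.5% |

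The sign reverses with the split. Under the planned effect, 25% loss on TJT and 15% on control, all with baseline only, gives 0.75 × 8.3 − 0.85 × 6.3 = 0.87 mmHg and 28% power. With equal loss and equal timing the null stays at 0.

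**The case against.** The strongest objection concerns the primary endpoint. Table 1 schedules blood pressure on days 3 and 21, so LOCF as written could carry a day-3 value forward. A reader might infer that everyone lost before day 14 is certain to get zero blood pressure change. The documents do not support that. Equally, they describe days 3 and 21 as telephone contacts and give no way of taking three sitting readings by telephone, so the existence of those values is unresolved. The zero-change statement is certain only for syndrome score and biochemistry.

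The largest figures come from an extreme case with an assumed split. This stands: if all loss falls after day 14, the distortion is small, and LOCF power (90%) even exceeds that of 115 completers (86%). Nor is the 20% a forecast. It is a planning allowance in a four-week trial with retention measures. It is also too strong to say that bias follows whenever drop-out differs by arm, because timing can offset amount and a plateau in blood pressure would leave little bias.

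Finally, a mixed model learns nothing after baseline from patients who have only a baseline value. For them it relies on missing at random, which outcome-related suspension criteria call into question. That limits the remedy but does not make LOCF the better sole method. A separate analysis plan could hold model details, but LOCF is a choice this protocol already states.

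**Conclusion.** The concern holds in this form. LOCF is fixed as the only ITT method in a design where its assumption of no further change is implausible. For syndrome score and biochemistry it imputes zero change in every drop-out. For blood pressure it dilutes a real effect even when loss is equal: 2.0 becomes 1.60 to 1.92 mmHg at 20% loss. It can also create or hide a difference when the amount or timing of loss differs by arm: 0.13 to 0.63 mmHg under no effect at 15% versus 25%, with type I error from about 5.5% to 18% (21% at SD 4.31).

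These are illustrative ranges for DBP that rest on the assumed splits, the assumed timing and 80% of the fall by day 14. They do not predict this trial's error rate. The protocol also does not rank ITT above PP, so a reader should not infer that the LOCF result is the declared primary estimate. PP is nevertheless the only alternative, and it drops non-completers. The change should be made; it is not a reason to doubt the trial as a whole.

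**What to change.** 1. Replace LOCF as the ITT method for blood pressure by a mixed model for repeated measures on the validly measured post-baseline clinic values, adjusted for baseline blood pressure and centre, estimating the day-28 difference.
2. Use multiple imputation for outcomes measured only on days 0 and 28.
3. Keep LOCF as a sensitivity analysis, and add one that departs from missing at random, because patients with baseline only contribute no post-baseline information to the model.
4. Reconcile Table 1 with the visit schedule: state whether blood pressure on days 3 and 21 is measured, how, and whether it enters the analysis.
5. Reconcile the Suspension criteria and the unblinding section with the ITT principle so that, unless consent is withdrawn, outcome data at the already scheduled day-28 visit are still sought from patients who stop study drug. This concerns data collection only and leaves the rules for stopping treatment as they are.

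The cost is revised analysis wording, consistent text in the schedule, suspension and unblinding sections, and a little more analysis work. The downside is reliance on missing at random in the main model, which the added sensitivity analysis is there to test.

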#### Plans to give access to the full protocol, participant-level data, and statistical code {31c}

The datasets used during the current study are available from the corresponding author on reasonable request.

## Oversight and monitoring

### Composition of the coordinating center and trial steering committee {5d}

#### Trial steering committee

The trial steering committee (TSC) and coordination center are composed of the principal researcher, leading researcher of each subcenter, and experts from the Ethics Committee of the Affiliated Hospital of Shandong University of Traditional Chinese Medicine. The coordination center and TSC are responsible for the quality control of clinical trials, assisting and supervising the completion of the ethical review of each subcenter, reviewing the progress of the study, and providing unified training for the assistant investigators, including filling out the CRF form, subject follow-up, and adverse event reporting and management. In addition, they are in charge of the interpretation of the results and the publication of study reports. The study team and the main researchers will meet every 3 months to supervise, review, and discuss the study progress.

#### Subcenter

Each subcenter has a trained cardiologist for the recruitment of potential recruits and a study nurse for collecting ECG and blood samples. A research associate and graduate student research assistants will help with signing informed consent, filling out the CRF form, and general local organization.

#### Coinvestigators

The coinvestigators are responsible for supervising the progress of the trial and reviewing adherence to the study protocol. They report the research progress to TSC every 3 months.

#### Composition of the data monitoring committee, its role, and reporting structure {21a}

The data monitoring committee will consist of a senior cardiologist, one mid-career cardiologist, and the statistician of the study center. After the data are completely collected, digital data will be cross-checked by cardiologists using paper CRFs. Severe adverse events will be the major task for the data monitoring committee. Only the statistician will check the finalized combined dataset.

#### Adverse event reporting and harms {22}

Adverse events include any symptom, syndrome, or disease that is present in a subject during the clinical study and would affect the subject’s health, as well as clinically relevant conditions found during laboratory or other diagnostic procedures. Researchers must record the time, duration, measures taken, and severity of AE in the common reporting format (CRF) table within 24 h of AE occurrence and report to the Ethics Committee. The researchers will evaluate the correlation with the drug under study and decide whether to discontinue the observation based on the condition, and the cases of drug discontinuation due to adverse reactions will be unblinding and followed. According to the clinical use of *Uncaria rhynchophylla*, *Semen Raphani*, and other traditional Chinese medicine decoction pieces and Val/Aml, we do not expect serious adverse events due to our intervention.

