#### Criteria for discontinuing or modifying allocated interventions {11b}

Discontinuation criteria are withdrawal of consent, subsequent occurrence of a suspension criteria criterion (e.g., use of prohibited drugs), lack of compliance, and medical problems for stopping the intervention.

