### Assignment of interventions: blinding

#### Who will be blinded {17a}

The following research team members are blinded to the care of the subjects: the clinical investigators, the research staff, and attending physicians.

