#### Procedure for unblinding if needed {17b}

The researcher can open the blinding code only when the subject has serious adverse events or other special or emergency events, which necessitates knowing the specific grouping of the subjects before treatment. Researchers should contact the ethics committee to report the reasons for unblinding and record the date of unblinding, treatment, and final results in the CRF form. The subjects should discontinue the study after unblinding. The main investigator will decide whether the research protocol needs to be revised according to safety data after unblinding.

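### The harms section unblinds every stop for an adverse reaction, against the need-to-know rule in the unblinding section, and unblinded patients then leave the study

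*Protocol article*

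**What the plan says.** Two sections of the protocol article set rules for opening the code.

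- *Procedure for unblinding if needed {17b}* is exclusive: "The researcher can open the blinding code only when the subject has serious adverse events or other special or emergency events", and the event must be one "which necessitates knowing the specific grouping of the subjects before treatment". It adds a consequence: "The subjects should discontinue the study after unblinding".
- *Adverse event reporting and harms {22}* has the researchers judge whether an event is related to the study drug and "decide whether to discontinue the observation based on the condition". The same sentence goes on: "the cases of drug discontinuation due to adverse reactions will be unblinding and followed". It names no level of severity and no need to know the arm.

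Four other places bear on the result.

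- *Who will be blinded {17a}* lists "the clinical investigators, the research staff, and attending physicians".
- *Criteria for discontinuing or modifying allocated interventions {11b}* includes "medical problems for stopping the intervention".
- *Primary outcomes* under {12} are the changes in sitting systolic and diastolic pressure from baseline to week 4.
- *Methods in analysis to handle protocol non-adherence and any statistical methods to handle missing data {20c}* states: "In ITT analyses, missing data will be supplemented by the last observation carried forward (LOCF) method".

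**The concern.** Section {22} makes stopping the drug for an adverse reaction a sufficient reason to open the code. Section {17b} does not. A site that follows {22} opens codes that {17b} forbids, among staff whom {17a} lists as blinded and who also judge causality.

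The consequence in {17b} then applies: the unblinded patient leaves the study. If that happens before week 4, the primary outcome is missing and LOCF supplies it, although an onsite week-4 visit is already scheduled. These patients are not a random subset, because they are selected by how well they tolerated the treatment. An imbalance between the arms, or an influence on the causality ratings of other patients, is possible, but nothing in the document shows either.

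**Working it through.** **The two rules side by side**

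| Question | {17b} | {22} |
|---|---|---|
| What opens the code? | A serious, other special or emergency event | Stopping the drug for an adverse reaction |
| Must the allocation be needed? | Yes | Not stated |
| What happens next? | The patient leaves the study | The patient is followed; kind and length not stated |

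Test case: a patient has a mild, self-limiting reaction and stops the tablets.

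- Under {22} the code is opened.
- Under {17b} it stays closed, because the event is neither serious nor an emergency and nobody needs the allocation in order to treat it. The undefined category of special events does not change this, since the need-to-know clause still limits it.

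The follow-up mentioned in {22} may mean safety follow-up only. It therefore need not contradict the instruction in {17b} to leave the study, but it does not secure a week-4 blood pressure either.

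**Scale**

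The plan states no figure on this point, so there is none to reproduce. The inputs are:

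- 288 patients at seven centres (*Study setting {9}*).
- DBP values of 8.3 mmHg (TJT) and 6.3 mmHg (control) from *Sample size {14}*, read here as falls. That section calls them values after treatment, so this reading is an assumption.
- A share *f* who stop for an adverse reaction. It is not in the document and is assumed to be 1% to 8%.

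Patients unblinded under {22}:

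- 288 × 0.01 = 2.9 and 288 × 0.08 = 23.0, so about 3 to 23.
- Per centre: 2.9 / 7 = 0.4 and 23.0 / 7 = 3.3.

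LOCF with baseline carried forward (change of 0) and the same *f* in both arms gives a difference of (1 − *f*) × (8.3 − 6.3):

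- *f* = 1%: 0.99 × 2.0 = 1.98 mmHg
- *f* = 8%: 0.92 × 2.0 = 1.84 mmHg

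Unequal rates matter more. If the stops occur only in the TJT arm, the difference is 8.3 × (1 − *f*) − 6.3:

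- *f* = 1%: 8.217 − 6.3 = 1.92 mmHg
- *f* = 8%: 7.636 − 6.3 = 1.34 mmHg

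The one-sided case only shows sensitivity. Nothing in the document points to such an imbalance.

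**The case against.** The strongest case against has four parts.

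1. **Narrow conflict.** {17b} also allows a code break for special events and does not define them. A related reaction that ends treatment in a patient with stage 2 hypertension could be read as one, and knowing whether TJT was taken may matter for later care. This holds for some patients. It does not hold for a mild reaction that can be managed without the allocation, and if every stop counted as special, the restriction in {17b} would do little.

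2. **Who learns the code.** {22} does not say who opens it, who is told, or when. That is correct, but {17b} gives the researcher this power, so sites can be expected to read {22} the same way. It is also fair that codes are individual, that the patient's treatment has already stopped, and that blood pressure is the mean of three electronic readings. All of this limits bias in the primary outcome.

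3. **Cause of the missing data.** Some of these patients may leave observation under {11b} or {22} whether or not the code is opened. This stands: the extra loss due to unblinding is unknown, and correcting the trigger alone might recover no week-4 value. The fix therefore has to reach the withdrawal rule as well.

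4. **Direction of the LOCF effect.** Carrying baseline forward is the extreme case. A patient who stops after the onsite week-2 visit carries forward an on-treatment value, and the error could then run the other way. This stands too. The calculation bounds shrinkage only, and its equal-rate range is 0.02 to 0.16 mmHg.

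That the article condenses a fuller protocol does not answer the main point: both rules are stated, and they disagree.

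**Conclusion.** The concern holds. The unconditional unblinding in {22} conflicts with the need-to-know rule in {17b}. Followed as written, it produces avoidable code breaks in a double-blind trial. Together with the instruction to leave the study, it can also turn a measurable week-4 primary outcome into an imputed one for patients selected by tolerability.

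The contradiction rests on the text alone and needs no assumption. Its effect on the result is probably small in a 4-week trial. The range of 1.98 to 1.84 mmHg against a planned 2.0 mmHg assumes 1% to 8% stopping, equal rates, no change carried forward, and the sample-size DBP values read as falls. With equal rates this is an upper limit on the shrinkage, because patients off the drug would probably show a smaller fall than their arm mean even if measured. Bias between the arms is possible but not shown.

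**What to change.** - In {22}, replace the automatic unblinding with the need-to-know rule of {17b}, so that stopping the drug for an adverse reaction does not by itself open the code. Emergency unblinding stays as it is.
- In {17b}, have unblinded patients stop study treatment instead of leaving the study.
- State that patients who are unblinded or off the drug return for the scheduled week-4 blood pressure and adverse-event assessment unless they withdraw consent.
- Optionally, report the number of code breaks by arm.

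The cost is a change of protocol wording and slight extra effort to retain a few patients for a visit that is already planned.
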